## Abstract

**Background:**

Domestic violence and abuse is threatening behavior, violence/abuse used by one person to control the other within an intimate or family-type relationship. Women experience more severe physical and sexual domestic violence and abuse and more mental health consequences than men. The current study aims at exploring of the role of hypothalamic-pituitary-adrenocortical axis activity in abuse impact on women's mental health. Study objectives: 1) To evaluate diurnal cortisol slope, cortisol awakening response, and the mean cortisol concentration in women with a current or recent experience of abuse; 2) To estimate whether cortisol secretion is associated with type, severity, duration and cessation of abuse; 3) To investigate whether cortisol acts as mediator between abuse and mental health condition; 4) To examine whether there is any distinction in cortisol levels between those women exposed to both childhood abuse and domestic violence and abuse and those experienced only the latter. 4) To explore whether cortisol secretion differs between women living in refuge and those still living in the community.

**Methods/Design:**

To meet study objectives 128 women will be recruited in a domestic violence agency and local communities. Baseline and 3-month follow-up measures will be taken over 6 months after recruitment. Each assessment will include: (1) standardized self-administered questionnaires to evaluate socio-demographics, experience of violence and abuse, mental and physical health; (2) weight and height measurement; (3) self-completion of wakening, post-wakening and evening saliva samples. Saliva will be analysed for cortisol and cortisone using Ultra performance liquid chromatography – tandem mass spectrometry.

We will compare diurnal cortisol parameters between non-abused controls and abuse survivors with and without mental health conditions. First following descriptive statistics for all the cortisol and mental health outcomes, relationships between them will be investigated using appropriate regression models. Second, these techniques will be used to investigate the extent to which cortisol measures act as potential mediators between type, severity, duration of abuse and mental disorders.

**Discussion:**

Results of the study will increase our understanding of the pathophysiological mechanisms of abuse-related mental health disorders in women and inform researchers and practitioners on the possibility of using salivary cortisol as a biological marker for prognosis, diagnosis, and treatment evaluation among abuse survivors.

**Trial registration:**

ClinicalTrials.gov registration NCT01632553

## Background

Domestic violence and abuse (DVA) is threatening behavior, violence or abuse (psychological, physical, sexual, financial or emotional) between adults who are or have been intimate partners or family members, regardless of gender and sexuality. DVA can be better understood as a chronic syndrome characterized not only by episodes of physical violence but also by the emotional and psychological abuse the perpetrators use to maintain control over their partners [1]. Life time prevalence of DVA is 28% for women and 18% for men, although severity and consequences of abuse are less for men [2]. Over and above damage to physical and reproductive health DVA has long-term detrimental effects on mental health for women consulting in primary care [3,4]. High prevalence of lifetime and past year DVA is reported in psychiatric female patients [5]. A meta-analysis of (mostly) North American studies measuring the relationship between DVA and mental disorders reported increased risk for depression, anxiety, psychosomatic disorders, posttraumatic stress disorder (PTSD), alcohol abuse, and suicidal behavior [6]. Compared to non-abused women, female victims of DVA visit their general practitioners more frequently. They are also more often referred to additional diagnostics and mental health care, as well as prescribed antidepressants [7]. Kernic et al. [8] have established that cessation of DVA among survivors is associated with decreased prevalence of depression; whereas Anderson and Sounders [9] have found that some women out of the abusive relationship may have greater psychological difficulties than those who are still in it. Blasco et al. [10] concluded that the pattern of mental health recovery depends on the type of DVA that the women had been exposed to.

In addition, the mechanisms through which DVA causes mental and physical conditions are very poorly studied. One mechanism that may contribute to stress-related disorders is the hypothalamic-pituitary-adrenocortical (HPA) axis, which produces cortisol [11-13]. Cortisol activity in healthy children and adults follows a consistent diurnal pattern with peak levels of output observed within the first 30–40 min after awakening followed by a progressive reduction throughout the morning and afternoon with a nadir around midnight [14]. Cortisol levels naturally increase in response to exposure to acute stress and helps organisms cope with a short term homeostatic challenges by modification of metabolic and cognitive function [15]. Chronic stress has the capacity to increase or decrease HPA activity, and the resulting pattern depends, both on features of the stressor and the person facing it. Female survivors describe DVA as traumatic uncontrollable stress that poses a threat to their physical and social self, and is associated with feelings of shame [16]. There are very few studies focused on assessing physiologic correlates of chronic stress in abused women.

Salivary cortisol has been successfully used as a biological marker of HPA axis activity in epidemiological studies [17,18] including samples of women exposed to DVA [19-21]. Diurnal cortisol slope, cortisol awakening response (CAR), and area under the daytime cortisol curve have been found the most robustly related to psychosocial phenomena and to health outcomes [22]. Systematic review of the endocrine sequelae in chronically stressed but non psychiatric caregivers for family members reveals four studies which reported no difference, five studies reporting increased cortisol output, and four studies reporting hypo- secretion of cortisol compared to controls [23]. Powell et al. [20] have found out that women chronically stressed by undergoing a divorce or separation displayed elevated evening salivary cortisol compared to no stressed women in stable marriages. Moreover, it was the chronic stress rather than depression or acute stress that accounted for the elevation of evening salivary cortisol. Systematic review and meta-analysis of cortisol and posttraumatic stress disorder revealed significantly lower cortisol levels in people with PTSD due to sexual or physical abuse than controls. Interestingly, no difference in cortisol levels was found between controls and people with PTSD due to other types of trauma [24]. In contrast, anxiety disorder was associated with higher awakening cortisol levels [25]. Meta-analysis of studies meeting methodological standards showed that depression was associated with small-to-moderate elevation in cortisol output [26].

Long-term studies are absent in the field of pathophysiology of DVA [22]. The results of existing cross-sectional and short-term longitudinal studies testing the impact of childhood abuse and DVA on women’s HPA axis functioning are contradictory (see Additional file 1).

It is evident that most investigators have reported different patterns of alterations in diurnal cortisol output in women exposed to childhood abuse (CHA) and DVA. However there are researchers who have concluded that cortisol is a marker of abuse exposure rather than mental health diagnosis [27,28]; others stated that alteration in cortisol output is a correlate of abuse-related mental disorder [29,30]. Currently, it is known that CHA influences the psychobiology of cortisol function and that there is a development from hyper secretion of cortisol to hypo secretion by early adulthood [14]. It is also known that both physical and psychological DVA have significant impacts on the neuroendocrine system of women [27]. At the same time it is not clear whether currently and recently abused women, who have abnormal diurnal cortisol profiles, demonstrate poorer mental health outcomes and how this may correlate with type, severity, duration and cessation of abuse. There is a hypothesis that DVA survivors may be characterized by alterations in HPA axis activity [31] and that further longitudinal studies are needed to identify specific stress system disturbances in this group [2,32]. The current research study aims to investigate the role of the HPA axis on the impact of DVA on women’s mental health. This study tests the hypothesis that compared to non-abused controls all abused women have altered diurnal rhythm in cortisol secretion and that the pattern of this alteration is predicted by abuse characteristics, such as its type, severity, duration, and cessation.

### Study objectives

1. To evaluate the key diurnal cortisol parameters (diurnal cortisol variation, CAR, and mean cortisol concentration) in women with a current or recent experience of DVA

2. To estimate whether cortisol parameters are associated with type, severity, duration and cessation of abuse

3. To investigate whether cortisol outcomes act as a mediator between the features of abuse and mental health state

4. To examine whether there is any distinction in cortisol levels between those women exposed to both CHA and DVA and those experienced only the latter

5. To explore whether cortisol secretion differs between women, living in a domestic violence refuge and those still living in the community (after adjustment for confounding effects of abuse severity and continuing contact with abuser).

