## Methods/Design

The study was approved by a Research Ethics Committee established by the NHS Health Research Authority (NRES Committee South West – Frenchay, REC reference 12/SW/0162 of 25 June 2012). This is a 6-month, prospective, observational study based on a convenience sample. We will recruit index participants from the pool of women referred to specialized domestic violence agency SURVIVE South Gloucestershire and Bristol for community outreach support or refuge accommodation by other agencies or self-referred. The SURVIVE agency is a charitable organization which provides a range of services to women who have experienced DVA, including three refuges for women with children, outreach support, community-based Freedom Program groups, Independent Domestic Violence Advisers, support phone line, and Information Sessions in South Gloucestershire, and Bristol UK.

Inclusion criteria for participants contain age ≥ 18 y.o. Exclusion criteria include inability to read English, current use of steroid-based medications, pregnancy, presence of pituitary and/or adrenal gland disorder, and symptomatic psychotic illness. No participant will be excluded on the basis of their disability, ethnicity, religion or sexual orientation.

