Exposure to abuse through the lifespan will be measured using two psychological instruments. First, cases of childhood abuse and neglect will be detected using the Childhood Trauma Questionnaire (CTQ). CTQ is a 28-item inventory that provides brief, reliable and valid screening for histories of abuse and neglect. The CTQ inquires about five types of maltreatment – emotional, physical, and sexual abuse, and emotional and physical neglect – with five items representing each type. Participants respond to a series of statements about childhood events, which are endorsed on a 5-point frequency scale (0 = “never true”, 4 = “very often true”). Item scores are then summed to produce scores that quantify the severity of maltreatment in each area and that can be compared to clinical data. Cut-off scores for detecting likely cases of abuse and neglect are also provided. The CTQ was validated with data from over 2,000 respondents, including both clinical and non referred groups [33]. Second, exposure to DVA from intimate partner and other family members will be measured using the Composite Abuse Scale (CAS). The CAS is a widely used self-report of behaviors that women describe as abusive by their partners [34]. It is an easily administered measure that provides standardized sub scale scores on four dimensions of DVA. It consists of 30 items presented in a six point format requiring respondents to answer “never”, “only once”, “several times”, “monthly”, “weekly” or “daily” in a twelve month period. The Severe Combined Abuse sub scale has 8 items that represent severe physical abuse items, all sexual abuse items, and physical isolation aspects of emotional abuse. The Emotional Abuse subscale has 11 items that include verbal, psychological, dominance and social isolation abuse items. The Physical Abuse subscale has 7 of the less severe physical abuse items and the Harassment subscale has 4 items that are about actual harassment. CAS is scored by summating the frequency scores of the 30 items. The 0–5 for each item thus gives a possible score for each sub scale. Cut-off scores to exclude women labeled abused incorrectly are provided. The CAS can give not only prevalence figures, but also associations with other physical and emotional co-morbidities. It has been used in specialized domestic violence agencies, general practice, antenatal clinics, emergency departments, and drug and alcohol clinics. The CAS has demonstrated good acceptability and reliability, with some evidence of criterion and external validity. To measure DVA duration an item is added to the CAS asking participants the length (“one occasion”, “up to 6 months”, “up to 1 year”, “up to 3 years”, “up to 5 years”, and “more than 5 years”) of abusive relationship.

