### Statistical analysis

For the sample size calculation we used findings from similar studies in comparable populations [24,43,44]. Thus, the number of participants required to detect a standardized difference in cortisol levels of 0.5 between abused women and non-abused controls with 80% power using a cut-off score for statistical significance of 0.05 is 128 (64 per group). Assuming 40% drop out rate before the study ends, around 213 eligible subjects would have to be approached. Assuming 60% response rate we will have to approach approximately 355 women, so 213 would consent to join the study, and of these 128 would be expected to complete the study.

Data will be coded and entered into research database during data collection by the two researchers responsible for recruitment. Stata software will be used for statistical analysis. All data will be checked for expected ranges, presence of outliers and abnormal values.

Sample will be analyzed by comparison of participant exposed to DVA and participants without DVA exposure on the basis of cortisol and mental health state data. Primary study outcome will be reported as diurnal cortisol variation, the degree of decline in cortisol across the day. Secondary study outcomes include CAR, size of post-awakening surge in cortisol that occurs in 30 minutes after awakening and mean salivary cortisol concentration across the day. As an additional measure of tissue cortisol the three saliva samples, awakening, post awakening, and bedtime, will also be assayed for cortisone.

Following descriptive statistics for all the cortisol and mental health outcomes, relationship between them will be investigated using appropriate linear (and, for binary outcomes, logistic) regression models. Using the CAS and CTQ data, these techniques will also be used to investigate the extent to which cortisol measures act as potential mediator between the type, duration and cessation of abuse and mental health condition for this group of women.

Missing data from women who dropped out of the study will be handled first by comparing their baseline variables with those who completed the study, and secondly using imputation techniques [45].

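### Objective 5 treats continuing contact with the abuser purely as a confounder, although it may partly result from where the woman lives, so the adjusted estimate can omit part of the refuge–community difference

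*Protocol article*

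**What the plan says.** The fifth objective in the protocol article (Study objectives) is "To explore whether cortisol secretion differs between women, living in a domestic violence refuge and those still living in the community", and the text in brackets after it adds "after adjustment for confounding effects of abuse severity and continuing contact with abuser". The objective itself therefore names two adjustment variables and gives both the role of confounder.

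Four other places bear on this:

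- **Methods/Design:** "This is a 6-month, prospective, observational study based on a convenience sample". Index women reach the agency "for community outreach support or refuge accommodation by other agencies or self-referred". Residence is therefore not randomised.
- **Background:** the study hypothesis is that "the pattern of this alteration is predicted by abuse characteristics, such as its type, severity, duration, and cessation". Objective 2 examines these same characteristics, cessation included.
- **Measurements:** the Composite Abuse Scale, which supplies abuse severity, asks about events "in a twelve month period".
- **Statistical analysis:** mediation is planned only for cortisol between abuse and mental health. Contact as a step between residence and cortisol is not considered.

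The Abstract states the refuge–community objective without any adjustment.

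**The concern.** A variable can be adjusted for as a confounder if it is not itself a consequence of the exposure. The word *continuing* points to contact at the time when the woman is already in refuge or still in the community. Separation from the abuser is a plausible consequence of refuge living, so current contact may lie on the path from residence to cortisol. The second half of that path is close to the study's own hypothesis, since the end of abuse is expected to predict cortisol. Cessation of abuse and absence of contact are not the same thing, but they are closely related.

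If so, adjusting for current contact changes the question from whether the two groups differ to whether they differ apart from contact. A report of no difference after control of confounding could then be taken to mean that residence is unrelated to cortisol, when women in refuge do differ because contact has stopped. The Discussion hopes that the results will clarify causal routes and help to direct intervention, so the label on this estimate matters.

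**Working it through.** **The plan's own figure.** The only stated sample size is for a "standardized difference in cortisol levels of 0.5 between abused women and non-abused controls with 80% power". With two-sided alpha 0.05 (two-sidedness assumed), the normal approximation is n = 2(1.96 + 0.84)²/0.5² ≈ 62.8, so 63 per group. The t-test version gives 63.8, so 64 per group and 128 in all, as stated. The inflation also agrees: 128/0.6 = 213 and 213/0.6 = 355. None of this concerns objective 5, for which no figure is given.

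**Set-up for objective 5.** Let d be the refuge–community difference not running through contact, b the shift in cortisol linked to contact, and pR and pC the proportions with contact in refuge and community. All are in SD units or proportions, and all are assumed. In an additive linear model with no unmeasured common cause of contact and cortisol:

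- overall difference = d + b(pC − pR)
- difference adjusted for contact = d
- share left out = 1 − d/(overall difference)

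**Results over assumed ranges.** With b from 0.3 to 0.8 and (pR, pC) of (0.1, 0.4), (0.1, 0.7) or (0, 0.8):

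| d | Overall difference | Adjusted | Share left out |
|---|---|---|---|
| 0 | 0.09 to 0.64 SD | 0 | 100% |
| 0.2, same direction | 0.29 to 0.84 SD | 0.20 SD | 31% to 76% |

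For example, with d = 0.2, b = 0.5, pR = 0.1 and pC = 0.7, the overall difference is 0.2 + 0.5 × 0.6 = 0.50 SD, and 1 − 0.2/0.5 = 60% is left out.

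**Precision.** With equal group sizes, the squared correlation of residence with contact is 0.25(pC − pR)²/[p̄(1 − p̄)], where p̄ is the mean of pR and pC. The variance inflation is 1/(1 − that value).

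- 10% v 50%: 0.25 × 0.16/0.21 = 0.190; inflation 1.24; SE up about 11%.
- 5% v 60%: 0.25 × 0.3025/0.2194 = 0.345; inflation 1.53; SE up about 24%.

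Any residual variance that contact explains would offset part of this loss.

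**The opposite causal order.** If contact came before the choice of residence and was not altered by it, the same quantity b(pC − pR) would be the bias in the unadjusted comparison, and the adjusted one would be right. The arithmetic cannot tell the two cases apart. Only the timing of contact relative to refuge entry can, and the article does not give it.

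**The case against.** The strongest reply is that the article never says when or how contact is measured, nor that refuge ends it. The comparison group is women in the community, not women still living with the abuser, and the index women have present or recent abuse, so some community women may already have left. The contrast in contact could be much smaller than in the illustrations. Residence is not randomised, and contact or threat before entry could drive both the route taken and cortisol. The adjusted contrast also answers a fair question, namely whether the refuge setting differs beyond severity and contact, and objective 2 covers cessation separately. Finally, an article need not list every model, and the Abstract's wording leaves room for an unadjusted comparison.

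Much of this stands. A reader might infer that contact is simply a mediator, that the adjusted result will be zero, or that contact should be taken out. The documents support none of these: complete removal follows only from setting d = 0, and leaving out pre-entry contact could exchange one bias for another. Nor do they support the inference that hardly any comparable women remain. Even at 5% v 60%, the no-contact stratum holds 95% of refuge and 40% of community women.

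What the reply does not remove is the label. The objective assigns contact the role of confounder without distinguishing contact before entry from contact during residence, and it does not say that the target is the difference apart from contact.

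**Conclusion.** The point holds in a limited form. Contact concurrent with residence is plausibly at least partly its result, so the estimate specified in objective 5 can omit the part of the refuge–community difference that runs through contact. That residence affects contact is inferred from the nature of the comparison; the article does not state it. The size cannot be determined from the article, and the figures above show only what would follow from assumed inputs. The contact-adjusted contrast is legitimate if it is described as the difference not explained by contact. The consequence is confined to one exploratory objective. The primary outcome, the comparison of abused with non-abused women and the sample size are untouched.

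**What to change.** Report two models for objective 5 side by side:

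1. Adjusted for abuse severity and other factors that precede refuge entry, including contact before entry where it is recorded. Present this as the overall difference by residence.
2. The same model plus current contact, labelled as the difference not explained by contact and not as control of confounding.

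Show the cross-table of residence by current contact beside them, so that the overlap can be judged. Severity should refer to the period before entry as far as the data allow, because the twelve-month window of the abuse scale may include time in refuge.

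The cost is one extra model and a change of wording; current contact has to be collected for objective 5 in any case. The drawback is that the first model may retain some confounding if contact before entry is not recorded, and the report should say so.
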